#### 4.5.2. Capsaicin challenge detailed schedule- Part A

The table below is based on an example randomization schedule for reference only. Each subject will be assigned an individual randomization schedule detailing which dose will be given in which order

| Procedure                           | Study Day (per treatment arm) |                |                |         |                |                |                |         |                |                |                |         |                |                |                |         |
|-------------------------------------|-------------------------------|----------------|----------------|---------|----------------|----------------|----------------|---------|----------------|----------------|----------------|---------|----------------|----------------|----------------|---------|
|                                     | Day 1 AM                      |                |                |         | Day 1 PM       |                |                |         | Day 2 AM       |                |                |         | Day 2 PM       |                |                |         |
|                                     | 0                             | 60 min         | 95 min         | 120 min | 0              | 60 min         | 95 min         | 120 min | 0              | 60 min         | 95 min         | 120 min | 0              | 60 min         | 95 min         | 120 min |
| Administration of SB705498 cream 1% | X                             |                |                |         |                |                |                |         |                |                |                |         |                |                |                |         |
| Administration of SB705498 cream 3% |                               |                |                |         | X              |                |                |         |                |                |                |         |                |                |                |         |
| Administration of SB705498 cream 5% |                               |                |                |         |                |                |                |         | X              |                |                |         |                |                |                |         |
| Administration of Placebo cream     |                               |                |                |         |                |                |                |         |                |                |                |         | X              |                |                |         |
| SB705498/Placebo wiped away         |                               | X              |                |         |                | X              |                |         |                | X              |                |         |                | X              |                |         |
| Assess area of flare using LDI      | X                 | X  | X  | X       | X  | X  | X  | X       | X  | X  | X  | X       | X  | X  | X  | X       |
| Capsaicin cream applied             |                               | X              |                |         |                | X              |                |         |                | X              |                |         |                | X              |                |         |
| Capsaicin wiped away                |                               |                | X              |         |                |                | X              |         |                |                | X              |         |                |                | X              |         |
| Pharmacokinetic sample              | X                             | X              | X              | X       | X              | X              | X              | X       | X              | X              | X              | X       | X              | X              | X              | X       |

1. Baseline scan will be performed before application of the SB705498 cream or Placebo
2. LDI scan will be performed after application of SB705498 cream or placebo. Cream is applied, left for 1 hr and excess is then removed to allow scanning.
3. LDI scan will be performed 5 mins after the Capsaicin cream is wiped off the arm.

**4.5.3. Part B**

| Procedure                                                | Screening
(up to 30
days prior
to Day 1)  | Study Day (per treatment arm) |    |    |       |             |    |    |       | Follow-up
(10-14 days
post-last
dose) |
|----------------------------------------------------------|----------------------------------------------------------------|-------------------------------|----|----|-------|-------------|----|----|-------|------------------------------------------------|
|                                                          |                                                                | Day 1                         |    |    |       | Day 2       |    |    |       |                                                |
|                                                          |                                                                | -30
mins                   | 0h | 1h | 1.25h | -30
mins | 0h | 1h | 1.25h |                                                |
| Admission to Unit                                        | X                                                              | X                             |    |    |       | X           |    |    |       |                                                |
| Consent review                                           | X                                                              |                               |    |    |       |             |    |    |       |                                                |
| Full Physical Exam                                       | X                                                              |                               |    |    |       |             |    |    |       |                                                |
| Brief Physical Exam                                      |                                                                |                               |    |    |       |             |    |    |       | X                                              |
| Medical/medication/
drug/alcohol history              | X                                                              |                               |    |    |       |             |    |    |       |                                                |
| Vital signs                                              | X                                                              | X                             |    |    |       | X           |    |    |       | X                                              |
| ECG                                                      | X                                                              | X                             |    |    |       | X           |    |    |       | X                                              |
| Urine Drug/Alcohol                                       | X                                                              | X                             |    |    |       | X           |    |    |       |                                                |
| Serum β-hCG (women)- Day 1 only                          | X                                                              | X                             |    |    |       | X           |    |    |       | X                                              |
| HIV, Hep B and Hep C screen                              | X                                                              |                               |    |    |       |             |    |    |       |                                                |
| Haem/Chem/Urinalysis tests                               | X                                                              |                               |    |    |       |             |    |    |       | X                                              |
| Capsaicin challenge                                      | X                                                  |                               |    |    |       |             |    |    |       |                                                |
| Assess area of flare using LDI                           | X                                                  |                               |    |    |       |             |    |    |       |                                                |
| Assess ITCH intensity (COVAS)                            | X                                                  |                               |    |    |       |             |    |    |       |                                                |
| Administration of SB705498
cream/Placebo  |                                                                |                               | X  |    |       |             | X  |    |       |                                                |
| Histamine challenge                          | X                                                  |                               |    |    |       |             |    | X  |       |                                                |
| Cowhage challenge                            | X                                                  |                               |    | X  |       |             |    |    |       |                                                |
| COVAS scale                                  |                                                                |                               |    | X  | X     |             |    | X  | X     |                                                |
| Adverse Event Review                                     | X                                                              | ←=====→                       |    |    |       |             |    |    |       | X                                              |
| Concomitant Medication Review                            |                                                                | ←=====→                       |    |    |       |             |    |    |       | X                                              |

1. COVAS will be measured continuously from 1-2 mins before application of challenge agent and for a maximum time of 15 mins post application.
2. Screening assessments for Part B will only occur if the period of time between Part A screening and Part B study visit 1 exceeds 60 days.
3. To be performed for new subjects that have not taken Part in Part A.
4. Application of the cream/placebo followed by challenge agent assessment will be performed twice on each day. i.e. 4 applications over the 2 days with both SB705498 and placebo and each challenge agent.
5. The days on which the cowhage and histamine challenges are performed may be swapped according to site logistics and at the investigators discretion.

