One common disease with pruritus as a key symptom is atopic dermatitis (AD), which is frequently described as "the itch that rashes." Intensely itchy patches form. These patches can be widespread or limited to a few areas. Scratching often leads to redness, swelling, cracking, "weeping" of clear fluid, crusting, and scaling of the skin. TRPV1 has been shown to be upregulated in AD-skin lesions, and the activation of TRPV1 causes the release of proinflammatory and pruritic mediators ([Steinhoff, 2004](#); [Hutter, 2005](#); [Imamachi, 2009](#)). The activation of TRPV1 leads to the release of substance P and subsequently upregulates neurokinin-1 receptor ([Velazquez, 2002](#); [Hutter, 2005](#)). Substance P can contribute to the development of neurogenic inflammation and pruritus, and neurokinin-1 receptor antagonists can suppress scratching behaviours ([Ohmura, 2004](#); [Yamaoka, 2007](#) and [Kawana, 2007](#)), [Yun, 2011b](#)) have shown that a novel TRPV1 antagonist (PAC-14028) can suppress scratching behaviours in a mouse model of AD, through the inhibition of TRPV1 activation. This suggests that the antipruritic effect of TRPV1 antagonist in AD may be explained, at least in part, by the suppression of substance P release.

SB705498 is a potent and selective antagonist at the TRPV1 receptor and has previously been explored for inflammatory pain, migraine and allergic and non-allergic rhinitis. Topical administration of SB705498 provides a means to examine the role of this mechanism on pruritus and hence it's therapeutic potential.

This proposed experimental medicine study will consist of two sections. Part A has been designed to establish whether the formulation is capable of delivering SB705498 to the proposed site of action, and to select an appropriate dose for Part B. Part B will examine the effect of SB705498 on pruritus initiated by a histaminergic and a non-histaminergic pathway, using two different challenge agents. This may provide important information about the role of TRPV1 in pruritus and the therapeutic potential of SB705498.

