#### **4.1.3. Part B**

Of the sixteen subjects randomised to participate in Part A, the ten subjects who show the most optimal treatment response during the capsaicin challenge compared to placebo will be asked to participate in Part B. If we are unable to obtain data from ten of the Part A subjects, we may ask the next best responders from Part A to go on to Part B or recruit new subjects to enter the study and participate in Part B of the study, providing they pass screening and challenge agent assessments.

Each volunteer will be randomised to receive the placebo and the selected topical application strength of SB705498 from Part A of the study for both the cowhage and histamine challenge. Each subject will participate in both a cowhage challenge and a histamine challenge with both treatment arms in a crossover fashion an example of a possible randomisation schedule is shown in Figure 2. Each subject will receive two doses of SB705498 over 2 days.

The cowhage challenge will be performed on a separate day to the histamine challenge.

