#### 4.1.4. Cowhage/ Histamine Challenge

Subjects will be randomised to receive either the SB705498 cream or placebo treatment first. This will be applied to the volar surface of the forearm followed 1 hour later by the cowhage/ histamine stimulant. Subsequently once all itch sensations have subsided the other treatment (placebo or SB705498) will be applied to the corresponding area on the other forearm and the same stimulant (cowhage/ histamine) will be applied as before.

This whole procedure will be repeated for the remaining challenge agent, cowhage/histamine on the following day allowing time for previous itch sensations to completely subside. For each challenge agent itch intensity will be rated using the COVAS scale as previously described commencing 1-2 mins before the challenge agent is applied.

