### Part B.

Subjects in Part B of the study will be randomised to one of the following sequences: E F E F, F E F E, E F F E or F E E F in a 1:1:1:1 ratio where one of these will be placebo and the other will be SB705498. The first letter in the sequence will be applied to the first application site as shown in [Figure 3](#). Each subsequent letter will be applied to the next application site. This ensures that the dose of SB705498 will be compared to placebo on the same area of the opposite forearm for both the histamine and cowhage test.

**Figure 3 Example Schematic of application Sites****Part A**[figure not shown]**Part B**[figure not shown]

\*Note: The days on which the Cowhage and Histamine challenges will take place are interchangeable.

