## **Part B**

Average itch will be analysed using a mixed effects model, fitting terms for treatment, period and stimulant, as fixed effects and subject as a random effect. No baseline will fit in the model since no itch is present until the stimulant is added. Point estimates and 95% percent confidence intervals for the difference between and placebo will be constructed using the appropriate variance structure.

Model and distributional assumptions underlying all analyses will be assessed by visual inspection of residual plots. Homogeneity of variance will be assessed by plotting the raw residuals against the predicted values from the model, whilst normality will be assessed using normal probability plots. Normality of the subject effect estimates from the random term will be assessed using a normal probability plot. Alternative statistical procedures will be considered should the model assumptions be violated.

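### Part B neither randomises nor balances the order of the cowhage and histamine days, so a difference in drug effect between the two itch pathways cannot be separated from a treatment-by-day effect

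*Protocol*

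**What the plan says.** **What is randomised.** Protocol Section 4.2 (Part B) assigns subjects to the cream sequences "E F E F, F E F E, E F F E or F E E F in a 1:1:1:1 ratio". Section 4.1.4 describes the same element: "Subjects will be randomised to receive either the SB705498 cream or placebo treatment first". Each sequence contains one active and one placebo application in its first half and one of each in its second half.

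**How stimulants are placed.** Section 4.1.3 states: "The cowhage challenge will be performed on a separate day to the histamine challenge". The Part B table in Section 4.5.3 shows cowhage on Day 1 and histamine on Day 2. Footnote 5 to that table allows a change: "The days on which the cowhage and histamine challenges are performed may be swapped according to site logistics and at the investigators discretion". The note to Figure 3 in Section 4.2 repeats this: "The days on which the Cowhage and Histamine challenges will take place are interchangeable". No visible text randomises or balances the order. By contrast, Section 7.3 has the screening challenges run in random order.

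**Where creams go.** Section 4.2 ties position in the sequence to application site, and within a day the two creams go to matching areas of the two forearms.

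**Aim and analysis.** Section 1.1 says: "Part B will examine the effect of SB705498 on pruritus initiated by a histaminergic and a non-histaminergic pathway". Section 6.1.2 tests active against placebo. Section 6.2.4 (Part B) plans a mixed model "fitting terms for treatment, period and stimulant, as fixed effects and subject as a random effect". It names no treatment-by-stimulant term.

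**The concern.** Each stimulant has a whole day to itself, so within a subject stimulant and day coincide. They can be told apart only if some subjects have cowhage first and others histamine first, and the comparison is clean only if chance or design decides who has which. Here the default is one order for everyone, and departures rest on logistics or judgement.

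Part B uses two stimulants because they act by different mechanisms, and Section 1.5.4 looks to the results to support later work in pruritic indications. Readers will set the two drug effects side by side. Suppose the cream appears to work against cowhage on Day 1 but not against histamine on Day 2. Under the default order that could be a property of the pathway. It could equally be a change in the drug effect from Day 1 to Day 2, since every sequence includes active cream on Day 1, or a difference between the Day 1 and Day 2 skin sites. No later analysis can recover the separation if all subjects had the same order.

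**Working it through.** **1. The plan's own figure.** Section 6.2.1 gives a difference of 2 points, variability 1.15 (0–10 scale), two-sided 5% and at least 90% power. Reading 1.15 as a within-subject SD (the protocol does not say), the standard error is SD × √(2/n), with n − 2 degrees of freedom:

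- n = 9: SE = 1.15 × √(2/9) = 0.542; 2/0.542 = 3.69; power 88.4%.
- n = 10: SE = 1.15 × √(2/10) = 0.514; 2/0.514 = 3.89; power 92.4%.

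So 10 reproduces. It concerns active versus placebo and does not depend on challenge-day order.

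**2. A plain day effect cancels.** If Day 2 scores are shifted by a constant g under both creams, the Day 2 active-minus-placebo difference is (active + g) − (placebo + g), and g drops out. It therefore also drops out of any difference between the Day 1 and Day 2 contrasts.

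**3. A treatment-by-day effect does not cancel.** Let C and H be the true drug effects on cowhage and histamine, and let d be the amount by which the drug effect on Day 2 differs from Day 1 for reasons unrelated to stimulant. The within-subject difference, histamine contrast minus cowhage contrast, is:

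- cowhage first: (H + d) − C = (H − C) + d
- histamine first: H − (C + d) = (H − C) − d

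With a proportion p having cowhage first, the average is (H − C) + (2p − 1) × d.

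| Cowhage first | 2p − 1 | Share of d in the between-pathway contrast |
|---|---|---|
| all | 1.0 | all of it |
| 12 of 16 | 0.5 | half |
| 8 of 10 | 0.6 | 0.60 to 0.71 after period adjustment |
| half | 0 | none |

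The formula is exact when the cream sequences are balanced within each order. Ten subjects over four sequences cannot be (taken here as 3, 3, 2, 2). Fitting subject, four periods, treatment, stimulant and treatment-by-stimulant to every possible 8:2 assignment gives 0.60 to 0.71, averaging 0.65. Every possible 5:5 assignment gives 0. In all these layouts the overall treatment effect has zero bias from day or from treatment-by-day.

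Site works the same way. Position in the sequence fixes the site, so the Day 1 and Day 2 pairs of sites differ, and d may stand for a site effect on drug response as well as a day effect.

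**4. The stimulant term.** If period has four levels and all 10 subjects share one order, the stimulant indicator is the sum of the period 1 and 2 indicators, or of the period 3 and 4 indicators. The fixed-effect matrix (subject, period, treatment, stimulant) then has rank 14 with 15 columns, so stimulant cannot be estimated. If period means only first or second application within a day, the matrix has full rank (13 of 13), but the stimulant term then absorbs the day effect. With four levels and an 8:2 split the term is estimable, but its variance relative to 5:5 is 1/(4 × 0.8 × 0.2) = 1.56.

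**The case against.** The strongest reply is that nothing the protocol plans to test is touched. The objective, endpoint, hypothesis, power calculation and model all concern active versus placebo. That contrast is made within subject, within day, with one stimulant and on matching forearm areas. Examining an effect on each of two pathways is not the same as ranking them, and no between-stimulant test is planned. All of this stands and limits the priority.

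A reader might infer that any between-pathway difference is confounded with study day, so that ordinary habituation, sensitisation or learning would produce it. The documents do not support that: such shifts cancel within each day unless they change the drug effect itself. A reader might also infer that confounding is always complete. It is complete only if every subject follows one order, and the protocol permits swaps. With swaps it is partial, but its extent is uncontrolled.

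The documents give no evidence that a treatment-by-day effect exists. Section 1.7.1 expects less than 10% of applied drug in plasma and each application uses a new site, which weakens the case for carry-over. Blinding of clinical staff makes it unlikely that swaps would follow the cream sequence. These points reduce the likely size of the problem but do not supply the missing separation.

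Two further points are fair. The non-estimable stimulant term depends on how period is coded, which the protocol does not define, and stimulant is a nuisance term for the primary test. Figures 2 and 3 are not visible and might show more about scheduling. The text around them nevertheless leaves the day order open.

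**Conclusion.** The point holds as a limited design weakness. Challenge-day order is set by a default and by discretion, so a descriptive difference in drug effect between the histaminergic and non-histaminergic pathways cannot be separated from a treatment-by-day or application-site effect. The separation is lost entirely under one common order. It is lost in part, and without control, if some subjects are swapped: about 0.65 of such an effect at 8:2. No absolute size can be given, because the documents contain no estimate of a treatment-by-day effect.

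The validity of the primary comparison, of either pathway's own active-versus-placebo result and of the 10-subject sample size is not in question. The conclusion assumes that the unseen figures add no rule on day order and that sites follow sequence position as Section 4.2 states. The 8:2 and 12:4 splits are illustrations, not figures from the protocol. The rank deficiency further assumes four period levels. Priority is minor to moderate: worth correcting because it costs little beforehand and cannot be repaired afterwards.

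**What to change.** Add the order of the two challenge days to the Part B randomisation list: five subjects with cowhage first and five with histamine first. Spread each group over the four cream sequences as evenly as possible. Two orders by four sequences make eight cells, so 10 subjects cannot fill them equally; one order could take 2, 1, 1, 1 and the other 1, 2, 1, 1. The 5:5 split is what removes the confounding, and this small imbalance does not bring it back. Replacement subjects should inherit the day order along with the cream sequence.

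Remove the discretion from footnote 5 in Section 4.5.3 and from the note to Figure 3, and show the day as assigned by the schedule. In Section 6.2.4, state how many levels period has, so that day and stimulant are separately estimable.

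The cost is a revised randomisation list and two small text changes, with no extra subjects, visits or procedures. The downside is practical: the site must have both challenge agents ready on both days and loses the freedom to rearrange them.
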